## **5 Study design and study procedure, sub-study 1**

### **Title: Oxytocin, couple interaction and wound healing in everyday life**

#### ***5.1 Questions***

Sub-study 1 investigates the influence of oxytocin vs. placebo on the instructed positive pair interaction, on parameters of the HHNA (salivary cortisol) and the ANS (salivary alpha amylase) and furthermore on the healing of a standardized suction blister wound.

#### ***5.2 Hypotheses***

We hypothesise *I)* that, compared to placebo, oxytocin a) enhances instructed positive couple interaction, b) reduces the activity of psychobiological stress parameters and c) accelerates wound healing. In further exploratory hypotheses, the mediating influence of partnership quality and the couples' everyday interactions on these effects will be investigated.

#### ***5.3 Main target parameters***

The main target parameter in sub-study 1 is the healing process, i.e. the reduction in size of a standardized suction blister wound on the non-dominant forearm one week after application. Furthermore, the immediate and delayed immune response to the application of the wound is recorded locally and systemically.

#### ***5.4 Study design***

Sub-study 1 will be conducted according to ICH-GCP and in a randomized double-blind design. A total of 4 study arms will be investigated, which differ as follows: Oxytocin + positive couple interaction, oxytocin + no instructed interaction, placebo + positive couple interaction, placebo + no instructed interaction. 25 pairs per study arm will be randomly assigned. The probability of allocation to one of the 4 study arms is 25%, and the probability of allocation to oxytocin or placebo is 50%.

##### **5.4.1 Research sample & power analysis**

100 heterosexual couples aged 25-45 years will be analyzed. Using G\*Power (Buchner, Faul, & Erdfelder, 1998), a sample size of N=76 was calculated for sub-study 1 with regard to the

main outcome variable "wound size" (see below) (effect  $f = .40$ ; power = .82,  $\alpha = .05$ ).  
The total N is set to  $N=100$  in order to be able to compensate for any dropouts.

#### 5.4.2 Inclusion and exclusion criteria

The subjects must fulfil the following *inclusion criteria*:

- Heterosexual couple
- Between 25 and 45 years old
- In a stable relationship for at least one year (maximum 15 years) and living together
- No children
- Willingness to attend three laboratory appointments and carry out independent measurements at home
- Be healthy, e.g. have no acute, chronic physical, neurological, psychiatric or somatic illnesses
- Be a non-smoker (up to 5 cigarettes per day)
- fluent German
- Women: have a regular menstrual cycle (between 24 - 35 days)

#### *Exclusion criteria*

- Indications that the participant is unlikely to comply with the test plan (e.g. unwillingness to cooperate)
- Participation in another clinical trial within the last 4 weeks prior to inclusion
- Skin disease
- Accident with neurological sequelae
- Allergies or a history of known hypersensitivity to one of the drugs used or their ingredients, or to drugs with a similar chemical structure
- UV-B irradiation in the last 3 months before the examination
- Taking medication
- Drug use, addiction or other illnesses that do not allow the person concerned to the nature, scope and possible consequences of the clinical trial
- Overweight or underweight
- Daily alcohol consumption ( $> 60g$  alcohol, equivalent to approx. 7.5 dl wine or 2 litres beer per day)
- No participation of the Investigator or his/her family members, employees or other dependent persons
- Women: Pregnancy (for instructions on the double barrier to prevent pregnancy, see subject information) or intention to become pregnant during the course of the study

- Women: Breastfeeding

These criteria are queried with the interested participants in a telephone interview. No personal details are recorded during this telephone interview, so that no personal data can be linked to the inclusion or exclusion criteria before the consent form is signed. An appointment for the study is arranged with interested and suitable test subjects, at which the inclusion and exclusion criteria are discussed again and the test subjects sign the declaration of consent.

For this study, it is essential that certain things are controlled, as these activities or factors influence the measured values and may make them unusable. For this reason, the test subjects were asked to follow the instructions bellow:

- Do not drink coffee or other caffeinated drinks (cola, energy drinks, etc.), black tea or alcohol on the afternoon of the first laboratory appointment (approx. from 3 pm),
- Do not engage in excessive sport on the day of the examination,
- Do not smoke immediately before the 1st laboratory appointment,
- No physical exertion (cycling etc.) immediately before the 1st laboratory appointment,
- Do not eat anything heavy immediately before the 1st lab appointment.

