***2nd laboratory appointment:***

24 hours after the first laboratory appointment, the couples visit the Dermatology Clinic of the University Hospital for a second time and wound fluid is taken again by the medical doctoral student under the supervision of [name] [name] for analysis of cytokines and TEWL.

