### 3rd laboratory appointment:

During the third laboratory appointment, the size of the wound is determined non-invasively. This appointment again takes place at the dermatology clinic. Afterwards, the couples receive a debriefing and the expense allowance (see Fig. 2).

[figure not shown]

Figure2 : Overview of the entire study program.

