### **5.7.2 Biological data**

The hormonal data (salivary cortisol) and the salivary enzyme alpha amylase will be analyzed in the psychobiological laboratory of the Department of Clinical Psychology and Psychotherapy of the Psychological Institute of the University of Zurich (Head: [name]. [name]).

The following parameters will analyzed as wound healing parameters:

- Size of the wound (photographed with measuring tape immediately after wound application and 7 days after wound application)
- Trans-epidermal Water Loss (TEWL; using an evaporimeter before wound application, immediately after removal of the epidermis, 24 hours after removal of the epidermis, 7 days after removal of the epidermis)
- Epithelialisation (by microscopy before wound application, immediately after removal of the epidermis, 24 hours after removal of the epidermis, 7 days after removal of the epidermis)
- Mediators of wound healing: cytokines in the wound fluid (TNF alpha, IL1, IL6; analysis of the wound fluid 1) from two blisters immediately after application of the suction blisters, 2) from two intact blisters 24 hours after application of the suction blisters).

The evaluation of the data on wound size, TEWL and epithelialization will be carried out in the Dermatology Department of the USZ. The cytokine concentrations are analyzed by the Cytolab laboratory ([name], [name]). All data will be analyzed in strict compliance with the anonymization of the subjects (see below).

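### Four of the five pre-visit behaviour rules in sub-study 1 cover only laboratory appointment 1, so the later TEWL, epithelialisation and cytokine readings are taken without them

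*Protocol*

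**What the plan says.** After the exclusion criteria in Protocol section 5.4.2, the plan states that "it is essential that certain things are controlled, as these activities or factors influence the measured values and may make them unusable". Five instructions to participants follow. Four of them name the first appointment:

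- caffeinated drinks, "black tea or alcohol on the afternoon of the first laboratory appointment (approx. from 3 pm";
- smoking immediately before it;
- exertion: "No physical exertion (cycling etc.) immediately before the 1st laboratory appointment";
- a heavy meal immediately before it.

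The remaining instruction is "Do not engage in excessive sport on the day of the examination", which does not say which examination is meant.

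Sub-study 1 has three laboratory appointments. Section 5.4.4 describes the second: "24 hours after the first laboratory appointment, the couples visit the Dermatology Clinic of the University Hospital for a second time", for wound fluid and TEWL. Of the third it says: "During the third laboratory appointment, the size of the wound is determined non-invasively". Section 5.7.2 gives the fuller measurement list. It places both TEWL and epithelialisation before wounding, immediately after the epidermis is removed, and then "24 hours after removal of the epidermis, 7 days after removal of the epidermis". Wound-fluid cytokines are sampled at wounding and at 24 hours. Wound size is photographed at wounding and at 7 days.

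**The concern.** The plan gives a measurement reason for the rules: these behaviours can disturb what is measured. The same measures are then read again at later visits to which four of the five rules do not extend. By their stated timing, the appointment 1 readings precede the first dose, so every wound reading that could show a treatment effect comes at appointment 2 or 3. A participant who follows the protocol exactly may cycle, smoke (up to five cigarettes a day is allowed at entry), drink coffee or eat heavily directly before either visit.

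At stake is the precision of TEWL and epithelialisation, which section 5.6.2 lists with wound size as dependent variables of wound healing, and of the 24-hour cytokines, which it treats as mediators.

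**Working it through.** The protocol attaches no figure to this point, so the check is a comparison of the rules with the measurement schedule.

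**Step 1: which visits the rules cover (section 5.4.2)**

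| Rule | Visit named |
|---|---|
| Caffeine, black tea, alcohol | first only |
| Excessive sport | day of the examination, no number |
| Smoking | first only |
| Physical exertion | first only |
| Heavy meal | first only |

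Four of five rules are limited to appointment 1, one of five is open, and none names appointment 2 or 3.

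**Step 2: whether another section extends them.** The descriptions of the second and third appointments and of the EMA period in section 5.4.4 set no conditions of this kind. Neither does section 5.6.3.

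**Step 3: when the measures are read (sections 5.6.2 and 5.7.2)**

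| Measure | Role | Around wounding (appointment 1) | 24 hours | 7 days |
|---|---|---|---|---|
| Wound size | main target parameter (5.3) | yes | no | yes |
| TEWL | dependent variable | yes | yes | yes |
| Epithelialisation | dependent variable | yes | yes | yes |
| Wound-fluid cytokines | mediator | yes | yes | no |

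There are six post-dose readings: one of wound size, two of TEWL, two of epithelialisation and one of cytokines (1 + 2 + 2 + 1 = 6). None is covered by the four numbered rules. Leaving out wound size, five remain (6 − 1 = 5). Section 5.4.4 mentions only wound size at the third appointment. That the 7-day TEWL and epithelialisation readings are taken there follows from the timing in section 5.7.2.

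**Step 4: comparison with sub-study 2.** The nearly identical list in section 6.4.2 refers to the laboratory appointment without a number, although women in that sub-study attend twice. No reason is given for the narrower wording in sub-study 1.

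**Step 5: can a size be given?** The only power statement for sub-study 1 (section 5.4.1) is for wound size: f = .40, α = .05, N = 76, power .82. As a four-group one-way ANOVA the noncentrality is f² × N = .16 × 76 = 12.16 on 3 and 72 degrees of freedom. That gives power .823, so the stated figure reproduces. It cannot be carried over to TEWL, epithelialisation or cytokines, for which the protocol gives no effect size, variance or power.

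**The case against.** **Appointment 1 is special.** It is more than a baseline reading. It includes the wounding, repeated mood and pain ratings, the first dose and the videotaped interaction, over about 2.5 hours. The authors may have meant the rules for that session, and the 3 pm limit suits its 5 pm start. This is plausible and explains why control is needed there. However, the reason the plan gives is the measured values, and it does not say that the later readings of the same measures are exempt.

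**Adjacent skin as reference.** Section 5.6.2 compares the wound at one week with neighbouring intact skin. A same-visit reference on the same arm could absorb part of any systemic effect at day 7. This stands. The section describes no such comparison for the 24-hour readings.

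**Stronger readings.** A reader might infer three things that the documents do not support:

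- *That later readings are unusable.* The plan says only that they may be, and does not say which values are affected.
- *That the stated power of .82 is eroded.* That figure belongs to wound size, probably the least sensitive of the measures. Any variance increase would be an assumption without an anchor in the protocol, and the planned sample is 100, not 76, although the surplus is meant for dropouts.
- *That the drug comparison is biased.* Allocation is randomised and double-blind, so behaviour before a visit has no evident reason to differ between oxytocin and placebo. Couples do know whether they were given the interaction task, so a difference between those arms is conceivable, but nothing in the protocol indicates one.

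**Unseen material.** The subject information is not shown and may contain further instructions. The protocol should still state the measurement condition.

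**Conclusion.** The point holds as an inconsistent measurement condition. Sub-study 1 controls four kinds of behaviour before appointment 1 and leaves them uncontrolled before the visits at which TEWL, epithelialisation and cytokines are read again. The expected consequence is avoidable noise in those measures.

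The size cannot be stated from the documents. The conclusion assumes that the plan is right that these behaviours affect the measured values, and that TEWL, epithelialisation and wound-fluid cytokines are among those values. For the main target parameter, photographed wound size, the effect is probably small. The trial's validity is not in question; this is an inexpensive improvement worth making.

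**What to change.** In section 5.4.2, replace the references to the first laboratory appointment with: each laboratory appointment at which wound measurements are taken. Define the day of the examination in the sport rule in the same way. Record any breach in the CRF at each of these visits. Because appointment 2 falls 24 hours after an appointment that starts from 5 pm, the 3 pm limit carries over to it. No clock time is given for appointment 3, so the limit there needs to be stated relative to the visit. If control is meant for appointment 1 only, the protocol should say why.

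The cost is small: participants follow the same rules before two more visits. There is one side effect. Appointment 2 falls within the five EMA days, so that day's saliva and self-report data would be collected under slightly different conditions from the other days. This can be noted as a limitation or handled with a day indicator in the EMA model.

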### 5.4.3 Recruitment

The test subjects are recruited via circular mail from the mailing list for the recruitment of test subjects of the Psychological Institute of the University of Zurich, the description of the study in public media (ronorp, 20Minuten, NZZ), notices and websites for the recruitment of test subjects and receive CHF 500 per couple as compensation for participation. All couples will receive individual feedback on their results. On request, couples will be given the option of psychological counselling at the Outpatient Clinic for Cognitive Behavioral Therapy and Behavioral Medicine at the University of Zurich.

- Subjects may terminate their participation in the study at any time without giving reasons and without any disadvantage.
- The principal investigator may terminate a subject's participation in the study after weighing up the risk/benefit ratio. Possible reasons are
  - Health problems and adverse events
  - Refusal to use the nasal spray regularly
- Reasons for stopping the nasal spray immediately include

- Pregnancy
- Hypersensitivity to oxytocin or an excipient of the nasal spray
- Participation in the study must be terminated in the following cases:
  - If it subsequently transpires that the required inclusion criteria do not apply or at least one exclusion criterion applies
  - Cancellation of the investigation

#### **5.4.4 Procedure**

After a telephone interview in which inclusion and exclusion criteria are clarified, the first laboratory appointment is arranged with interested test subjects. After reading the information and signing the written declaration of consent at the first appointment, the participants receive a participant code and are given an individualized link to the study website. This link will take the subjects to a survey including questionnaires on personality, relationship quality, and chronic stress, which they can complete online. The online presentation of the questionnaires is organized via "Unipark" ([www.unipark.com](http://www.unipark.com)), a program for individualized scientific online data collection. Access to the electronic program "Unipark" and thus to the data of the participant is password-protected, and only the study coordinator has access. "Unipark" was specially designed by Globalpark AG for online research and administration of research data sets. The use of the program requires a license. The electronically collected data are only relevant in connection with the data collected in the laboratory. The electronic and laboratory data are merged using the respondent code, which the respondents receive at the first laboratory appointment and enter at the start of the online questionnaire. The merging of the electronic and laboratory data only takes place after the written declaration of consent, which the test subjects date and sign in the laboratory. If this is not done or the experiment is cancelled, the electronic data will be destroyed immediately. The data on the handheld computer cannot be viewed directly and is sent to a password-protected e-mail address and managed from there. Only the study management has access to this e-mail address.

#### ***1st laboratory appointment:***

The first laboratory appointment takes place at the Dermatological Clinic of the University Hospital Zurich in the evening from 5 pm.

[figure not shown]

Figure 1 : Flow chart, 1st + 2nd laboratory appointment

### Study information and declaration of consent:

Before the start of the study, the study participants are once again informed about the procedure and aim of the study on the basis of the subject information. It is also explained to them that pregnancy excludes participation.

### Admission procedure:

Study participants are asked to give their voluntary consent in writing. The investigator may only begin the study-specific examinations once the declaration of consent has been received. The enrolment examination is carried out according to the following criteria:

- Assignment of a subject number (in ascending order)
- Review of the inclusion and exclusion criteria
- Multi-drug test (urine test)
- For women: last menstruation + pregnancy test (standard urine test)

### Subject code

The respondents are assigned an individual code, which they are asked to enter later at the beginning of the online questionnaire.

**Suction bubble application**

If there are no objections to the subjects' participation, all inclusion criteria are met and there are no exclusion criteria, they are asked how they feel. A doctoral student in dermatology then applies standardized suction blister wounds to the forearm under the supervision of the investigator [name] [name] (both partners receive the suction blisters). During this procedure, the couples are informed about the second laboratory appointment, the momentary assessment part of the study, and the positive/negative couple interaction. Mood and pain perception are repeatedly recorded.

**Oxytocin/placebo administration + interaction**

After application of the wound, cytokine measurement 1 is performed and TEWL is measured. The test subjects are then given intranasal double-blind placebo or oxytocin (24IU, 3 sprays per nostril; both partners receive either placebo or oxytocin). The positive couple interaction is then explained and practiced. During this exercise, the couples are recorded on video. The first session lasts approximately 2.5 hours (see Figure 1).

**Ecological Momentary Assessment (EMA):**

For five days after the first laboratory appointment, the subjects are asked to chew saliva vials at 6 times/day to determine salivary cortisol and alpha-amylase levels (see Fig. 2). Four times a day, they were asked about stress, affect, and social interactions using a handheld computer. The confidentiality of the data on the handheld computer is guaranteed, as the data cannot be read directly on the device and is sent to a password-protected e-mail address to which only the study management has access. During laboratory session 1, the couples are shown how to take the nasal spray independently during the EMA and how to carry out the instructed couple interaction as well as the saliva and well-being measurements at home following a signal from the handheld computer. The saliva and well-being measurements are carried out at home on all 5 days, while the pair interactions should only take place on 3 evenings, at the couple's discretion.

***2nd laboratory appointment:***

24 hours after the first laboratory appointment, the couples visit the Dermatology Clinic of the University Hospital for a second time and wound fluid is taken again by the medical doctoral student under the supervision of [name] [name] for analysis of cytokines and TEWL.

### 3rd laboratory appointment:

During the third laboratory appointment, the size of the wound is determined non-invasively. This appointment again takes place at the dermatology clinic. Afterwards, the couples receive a debriefing and the expense allowance (see Fig. 2).

[figure not shown]

Figure2 : Overview of the entire study program.

## 5.5 Psychological examination methods

### 5.5.1 Self-report data

Self-assessed health (General Health Questionnaire, GHQ-12, Banks, 1983), personal information (standardized anamnesis questionnaire on housing and living situation, socioeconomic status, etc.), partnership quality (partnership questionnaire, PFB, Hahlweg, 1996), dyadic coping (Dyadic Coping Inventory, DCI, Bodenmann, 2008), social support (Dyadic Coping Inventory, Bodenmann, 2008), and social support (Dyadic Coping Inventory, Bodenmann, 2008).), relationship quality (Partnership Questionnaire, PFB, Hahlweg, 1996), dyadic coping (Dyadic Coping Inventory, DCI, Bodenmann, 2008), social support (Berlin Social Support Scales, BSSS, Schwarzer & Schulze, 2000), personality traits (NEO-FFI, Borkenau & Ostendorf, 2008), chronic stress (Trier Inventory of Chronic Stress, TICS, Schulz, Schlotz & Becker, 2004), resilience (Resilience Scale, RS, Schumacher et al., 2004) and functional

somatic complaints (Screening for somatoform disorders 7T, SOMS-7T, Rief & Hiller, 1996) as well as functional somatic syndrome (FSSS, Gaab et al., 2003) are recorded online via personalized access after the first laboratory appointment.

During the laboratory appointments, mood (positive affect - negative affect, PANAS, Krohne et al., 1996) and pain (visual analogue scale) are repeatedly assessed.

### **5.5.2 Standardised instruction of pair interaction**

During the first lab session, couples will either receive instructions for a standardized positive couple interaction or instructions to document a comparable time spent together during the coming week (without instructions on how to interact during this time).

50 couples are asked to rate 22 pre-defined positive or negative areas with regard to their relationship on a 4-dimensional Likert scale. They are also encouraged to add other areas not on the list. They are then asked which are the two most relevant positive or negative issues in their relationship and to discuss these. During this discussion, the couples are recorded on video. During three further, freely defined time points, the couples are asked to match the positive topics of the standard interaction to a recent interaction in everyday life. Couples in the control condition for this condition are asked to document the time they have spent together using the handheld computer.

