#### **4.2.3 Oxytocin, couple interaction and wound healing**

Wound healing can be interpreted as a sign of healthy immune function and thus of health in general. It involves three phases: 1) the inflammation phase, in which cytokine levels (interleukins 1 and 6: IL-1, IL-6), tumor necrosis factor  $\alpha$  (TNF- $\alpha$ ), and IL-8 increase in the wounded tissue, 2) the proliferation phase, which is characterized by the recruitment and replication of cells necessary for tissue and capillary regeneration, and 3) the epithelialization phase with collagen synthesis (Clark, 1996).

In addition to various factors that influence wound healing, such as age, gender, vitamin and trace element deficiencies (vitamin C, vitamin A, zinc) and systemic diseases (e.g. diabetes) (see Clark, 1996), there is evidence that chronic stress inhibits wound healing (for a review see Christian et al, 2006; DeVries et al., 2007) by slowing the production of pro-inflammatory cytokines (e.g. IL-1 $\beta$  and IL-6) in the wound through increased glucocorticoid (cortisol) concentrations (Hubner et al., 1996; Padgett et al., 1998). For example, Kiecolt-Glaser et al. (2005) found that negative pair interaction, as opposed to social support, slows wound healing in the laboratory. Interestingly, the group around DeVries (Detillion et al., 2004) was able to show in various studies with hamsters that social isolation causes an increased cortisol concentration and that treatment with oxytocin can in turn reduce cortisol and accelerate wound healing. This effect has not yet been investigated in humans.

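### Section 5.5.2 lets couples in the positive-interaction arms choose and discuss negative relationship issues, which contradicts the arm definition and the rest of the protocol

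*Protocol*

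**What the plan says.** Section 5.4 defines the four arms of sub-study 1: "Oxytocin + positive couple interaction, oxytocin + no instructed interaction, placebo + positive couple interaction, placebo + no instructed interaction". It adds that "25 pairs per study arm will be randomly assigned".

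Section 5.5.2 opens in agreement with this: "couples will either receive instructions for a standardized positive couple interaction or instructions to document a comparable time spent together". The detailed instruction then changes. First, "50 couples are asked to rate 22 pre-defined positive or negative areas with regard to their relationship", and they may add areas of their own. Next, "They are then asked which are the two most relevant positive or negative issues in their relationship and to discuss these", while being filmed. For three further occasions of the couple's choosing, "the couples are asked to match the positive topics of the standard interaction to a recent interaction in everyday life".

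Section 5.4.4, under the suction blister heading, says couples are informed during blistering about "the momentary assessment part of the study, and the positive/negative couple interaction". The next part of 5.4.4, on nasal spray and interaction, says that the positive interaction is explained, practised and filmed after dosing. Sections 5.6.1 and 5.7.1 likewise refer only to the standardised positive interaction. The table of contents includes the word positive in the title of 5.5.2; the heading in the body omits it.

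**The concern.** The content of one of the two crossed factors is not fixed. The arm name, the expectation in section 4.1 that positive interaction helps healing, and hypothesis (a) in section 5.2 all require positive content. The instruction that staff would apply allows either valence, at the couple's choice and after allocation.

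Three things are at stake:

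- **The interaction factor.** Its active level could mix positive and negative discussions, so a difference from no instructed interaction would lack a clear meaning.
- **Its combination with oxytocin.** Section 4.1 makes this the central question of the project.
- **Hypothesis (a).** It says that oxytocin enhances the instructed positive interaction. Section 5.4.4 places the exercise after the spray. If topics are chosen at that point, the choice is itself behaviour that the drug could influence. More positive behaviour on video could then reflect the choice of an easier topic rather than better interaction on a fixed positive task.

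**Working it through.** The point rests on comparing text, with little arithmetic.

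**The plan's own figure.** Section 5.4.1 gives N = 76, f = 0.40, alpha = 0.05 and power 0.82 for wound size. A one-way analysis of variance with four groups has numerator df 3, denominator df 76 − 4 = 72 and noncentrality f² × N = 0.16 × 76 = 12.16. Its power is 0.823, which reproduces the stated value. A single two-level effect (numerator df 1) gives 0.931 and does not match. The sample-size figure is therefore not at fault, and it is consistent with a calculation over the four arms, which include the interaction factor.

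**Who receives the instruction.** Two of the four arms carry the positive interaction: 2 × 25 = 50 couples, the number in 5.5.2. The wording therefore governs both instructed arms in full.

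**The passages side by side.**

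| Place in the protocol | Valence of the task |
|---|---|
| 4.1, 5.2, 5.4 | positive only |
| 5.5.2, opening sentence | positive only |
| 5.5.2, list of 22 areas | positive or negative |
| 5.5.2, issues chosen and discussed | positive or negative |
| 5.5.2, three home occasions | positive topics |
| 5.4.4, suction blister part | positive/negative |
| 5.4.4, spray and interaction part | positive only |
| 5.6.1, 5.7.1 | positive only |

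**Following the text literally.**

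1. A couple in a positive-interaction arm rates the list and names its two most relevant issues. Nothing in 5.5.2 prevents both from being negative.
2. They discuss those two issues on video. This is not the task that 5.4, 5.4.4, 5.6.1 and 5.7.1 name for that arm.
3. At home they are to draw on the positive topics of that discussion. They have none, so the home step cannot be carried out as written.

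**Share of the intervention.** There is one laboratory session and three home occasions, four in all. The contradictory wording governs the laboratory session directly. It reaches the home occasions only for a couple that chose no positive topic.

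**What cannot be computed.** The protocol gives no figure for the share of couples who would choose negative issues, and none for the effect of such a discussion relative to no instruction.

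**The case against.** **Positive content is plainly intended.** Sections 5.4, 5.4.4 (spray and interaction part), 5.6.1 and 5.7.1 all say so, as does the opening of 5.5.2. The text also shows signs of rough translation, such as a German fragment left in 6.5.1, so the stray wording may be a leftover or a translation fault. This settles the intent, but the conflict remains. Section 5.5.2 is where topic selection is described, and the double valence appears there twice and again in 5.4.4.

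**The rating list need not be wrong.** A checklist with both valences is compatible with the arm if only positive topics are then selected. This stands: the conflict lies in the selection and discussion step.

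**The analysis named for wound healing is untouched.** Section 5.7.3 lists oxytocin versus placebo and men versus women as the group differences. Oxytocin and placebo couples receive the same instruction under randomisation. This stands and limits the reach of the point.

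**Two stronger readings are tempting.**

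- A reader might infer from section 4.2.3 ("negative pair interaction, as opposed to social support, slows wound healing in the laboratory") that a negative discussion would pull healing in the opposite direction and cancel the arm effect. The comparison there is with social support, whereas this trial's control is no instructed interaction. Section 7 attributes the delay in particular to hostile interaction, and discussing a negative issue is not shown to be hostile.
- A reader might also put a percentage on the dilution by assuming a share of negative-topic couples. Any such share would be invented, and the calculation would treat one of four sessions as the whole intervention.

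**Conclusion.** The protocol is wrong as written on this point. The selection and discussion step in 5.5.2 and the phrase in the suction blister part of 5.4.4 contradict the arm definition in 5.4, the positive task in the rest of 5.4.4, 5.6.1 and 5.7.1, and the home step within 5.5.2 itself.

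The consequence is a possible blurring of the interaction factor, its combination with oxytocin, and hypothesis (a). It depends on the instruction being applied literally and on some couples choosing negative issues. The size cannot be derived from the document: the instruction covers 50 of the 100 couples, and the number who would choose negative issues is unknown. The documents do not support a claim that the arm effect would be reversed or cancelled, or that the oxytocin-versus-placebo comparison is biased.

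The correction should precede instruction of the couples, because analysis cannot restore a positive task that was not delivered.

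**What to change.** - In 5.5.2, state that the two issues chosen for discussion are positive ones, and that this also applies to any area the couple adds.
- In the suction blister part of 5.4.4, drop the reference to negative interaction so that the task is called the positive couple interaction, as in 5.4, the rest of 5.4.4, 5.6.1 and 5.7.1.
- The list of 22 areas may keep both valences, provided that only positive topics are selected from it for discussion.

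The cost is a wording amendment and a revised instruction sheet. No visits, staff or participants are added.
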